## Abstract

**Background:**

Movement-related behaviours, including prolonged sedentary behaviour, physical inactivity, and poor sleep, are associated with worse functional outcomes poststroke. Addressing these co-dependent behaviours early after stroke may help to optimize recovery and improve overall quality of life for individuals with stroke.

**Objective:**

This study aims to determine the feasibility and effect of a ‘sit less, move more, sleep better’ program early after stroke on functional mobility and global disability outcomes, while also exploring imaging and behavioural markers that may influence walking recovery.

**Methods:**

The study is an assessor-blinded, single-center, parallel-group, randomized controlled trial to be completed within 24 months from July 12, 2023 to June 30, 2025. We will enroll 50 patients with acute ischemic stroke within 7 days from symptom onset, aged 18 years or older, and with ongoing walking goals. Demographic and stroke characteristics, including stroke risk factors, neuroimaging, and acute stroke treatments, will be determined and documented. All participants will wear an accelerometer for one week at three different time-points (baseline, 6, and 12 weeks) to assess movement-related behaviours. Following randomization, participants in the intervention arm will receive a ‘sit less, move more, sleep better’ program for up to 1 hour/day, 5 days/week, for 6 weeks to enhance self-efficacy for change. Participants in the control arm will receive usual inpatient and early supported stroke discharge care. The feasibility outcomes will include reach (enrolled/eligible), retention (completed/enrolled), adverse events, and program adherence. Other outcomes at 6 and 12 weeks include the modified Rankin Scale, Timed-Up and Go, movement-related behaviours, walking endurance, gait speed, cognition, stroke severity and quality of life. Mixed-effects models will assess changes in outcomes over time. Compositional associations between movement-related behaviours and outcomes will consider covariates such as imaging markers.

**Discussion:**

Adopting a whole-day approach to poststroke rehabilitation will provide valuable insights into the relationship between optimizing movement-related behaviours early after stroke and their impact on functional outcomes. Through exploring person-specific behavioural and imaging markers, this study may inform precision rehabilitation strategies, and guide clinical decision making for more tailored interventions.

**Trial registration:**

Clinical Trial registration (ClinicalTrials.gov Identifier: NCT05753761, March 3, 2023).

## Background and rationale

The main aim of rehabilitation is to enhance recovery trajectories and improve adaptation to the loss of neurologic function, with the goal of promoting function and preventing stroke recurrence [1]. Stroke is a heterogeneous disorder characterized by diverse brain and behavioural changes, as well as varied rehabilitation outcomes among survivors. This heterogeneity presents a significant challenge when attempting to employ a “one-size-fits-all” approach to stroke rehabilitation [2]. Integrating knowledge about mechanisms of stroke recovery, biomarkers, and motor outcomes is a key challenge to inform individualized care and the development of targeted interventions.

Motor recovery begins early after stroke through neuroplasticity, with the greatest improvements occurring within the first 3 to 6 months after injury [3,4]. Therefore, optimizing rehabilitation during this critical window of recovery is important to enhance the recovery process. Preclinical animal studies have shown that more task-specific reaching movement repetitions are associated with better functional recovery after stroke, with upwards of 600–700 repetitions per day suggested in models with the most severe impairments [5]. However, the optimal dosage of stepping repetitions for humans is still undetermined. Moreover, people with stroke are largely sedentary throughout their acute and inpatient rehabilitation journey [6,7]. In our previous study, we showed that people with stroke, following inpatient rehabilitation and transitioning back to the community, spend approximately three-quarters of their waking hours in sedentary behaviour, and half of the participants have long sleep durations exceeding 9 hours per day [8]. Subsequently, we demonstrated that it is feasible to enhance self-efficacy and decrease sedentary time after stroke [9].

To inform personalized stroke rehabilitation, accelerometry may be utilized in addition to clinical outcomes to understand daily movement-related behaviours (sleep, sedentary behaviour, and physical activity) that influence stroke recovery. The use of wearable activity sensors enables unsupervised, continuous, and objective monitoring of performance during and outside structured therapy [10]. By recording exercise and non-exercise tasks over the whole day, a representative and reliable account of performance is obtained with minimal therapist burden. Studying whole-day movement-related behaviours can provide valuable insights into the complex interplay of the 24-Hour Activity Cycle [11]. Clearly, increasing time spent in one behaviour displaces time in the other behaviours within a 24-hour period [12]. For instance, dedicating more time to physical activity necessitates reducing time spent sleeping or engaging in sedentary behaviour, or both. Gaining insight into these relationships is crucial for targeted care, as they are predictors of recovery and health outcomes [13,14]. Employing a whole-day approach that maximizes stepping time and repetitions, frequently interrupts sedentary behaviour, and optimizes sleep may be beneficial.

Behaviour change is a complex process. To achieve success with interventions targeting behaviour change, it is crucial to systematically and rigorously design and develop the intervention, with a strong theoretical foundation as the basis. We previously developed a behaviour change intervention using social cognitive theory—a universally accepted and widely adopted theoretical framework for promoting behaviour change among people with stroke [15,16]. Social cognitive theory employs the concept of ’triadic reciprocal determinism,’ which asserts that each behaviour is influenced by the relationship between personal factors such as cognition and mood, environmental factors like peer influence and societal norms, and the behaviour itself [17].

In addition to behavioural outcomes, an understanding of novel imaging biomarkers may also guide intervention development for personalized stroke rehabilitation. In addition to cortical infarct volume, leukoaraiosis or cerebral white matter disease, recognizable on magnetic resonance imaging (MRI) as areas of hyperintensities [18] has gained significance as a potential moderator of stroke recovery [19–21]. In older adults, leukoaraiosis is associated with impairments in gait parameters, including step length and cadence, possibly due to ongoing axonal changes [22,23]. After a stroke, the impact of leukoaraiosis becomes more evident [24], possibly due to a diminished capacity of the cerebral tissue to respond to the brain injury [25]. For example, following mechanical thrombectomy poststroke, only 24% of patients with severe leukoaraiosis had a “good” 90-day modified Rankin Scale (mRS) score compared to 85% of patients without leukoaraiosis [21]. To date, there are no known therapies to slow the progression of leukoaraiosis and no rehabilitation interventions have been specifically developed for survivors of stroke with leukoaraiosis. Understanding the role of leukoaraiosis as a moderator of stroke recovery may help to identify individuals that may benefit from a different approach to rehabilitation through the whole-day strategy. We hypothesize that a whole-day rehabilitation approach will optimize movement-related behaviours and improve functional mobility after stroke, moderated by the extent of cortical infarct volume and leukoaraiosis.

## Methods

### Study design and setting

The study is an assessor-blinded, single-center, parallel-group, randomized controlled trial. The Standard Protocol Items: Recommendations for Interventional Trials (SPIRIT) guidelines will be followed for this study [26]. The study has received ethics approval from the Human Research Ethics Board at the University of Alberta (Pro00127990, February 3, 2023) and the protocol has been registered on the clinical trial registry (www.ClinicalTrials.gov ID: NCT05753761, March 3, 2023). Written informed consent will be obtained from the potential participant. The schedule of enrolment, interventions, and assessments is shown in Fig 1. The study will be conducted at the University of Alberta Hospital in Edmonton, Alberta, Canada and is anticipated to be completed within 24 months beginning from July 12, 2023 to June 30, 2025.

**Fig 1 pone.0290515.g001:**
[figure not shown]
Study schedule. BIG STEPS, Behaviour and Imaging Guided Stepping Training Early Post-Stroke.

### Patient population and eligibility criteria

Eligible participants will be within 7 days of ischemic stroke onset, aged 18 years or older, deemed medically stable by physicians, and able to walk at least 5 meters with or without a gait aid and minimal assistance from 1-person, and able to understand and follow instructions. Additionally, eligible participants will have ongoing mobility deficits such as foot drop, knee buckling, or gait asymmetry or other walking challenges such as walking speed below 1.0 meters per second. Potential participants will be identified by their physical or occupational therapists based on our eligibility criteria. Once a potential participant agrees to study participation, the research team will further screen for eligibility including mobility limitations and appropriateness for the study. Exclusion criteria include previously diagnosed mobility-limiting conditions such as multiple sclerosis or Parkinson’s disease, or if they have active cancer, uncontrolled high blood pressure, or an unstable cardiovascular condition. Rehabilitation team leads and care management staff will assist in study recruitment by distributing consent to contact forms to potential participants. After receiving informed consent, information regarding demographics (e.g. race/ethnicity), stroke characteristics, risk factors, infarct location and volume, and acute stroke treatments received (e.g. thrombectomy) will be determined and documented. Subsequently, participants will be set up to wear an activPAL accelerometer for one week, validated in stroke and that accurately distinguishes sedentary from non-sedentary behaviours [27]. The activPAL will be worn on the less affected thigh, separated from the skin by a soft cotton pad, and secured with a transparent film dressing to follow a 24-hour protocol.

## Interventions

### Experimental group: Behaviour and Imaging-Guided Stepping Training Early Post-Stroke (BIG STEPS)

In addition to standard of care management for ischemic stroke according to the Canadian Stroke Best Practices Guidelines [28], participants allocated to the experimental group will receive a ‘sit less, move more, sleep better’ intervention focused on reducing and frequently interrupting sedentary time, taking more steps, and sleeping better. Data acquired from the baseline activPAL monitoring for 7 days will be discussed with the participants and used to inform personalized whole-day activity and behaviour-change recommendations, including replacing prolonged sedentary periods with stepping time, and promoting better sleep. Fig 2 shows examples of outputs from the activPAL monitor before and after a behaviour change intervention focused on reducing and interrupting sedentary behaviour throughout the day. Guided by the Social Cognitive Theory framework [29], behaviour-change coaching sessions, outside of structured therapy, will be conducted in person or virtually (where applicable), for up to 1 hour a day, 5 days a week for 6 weeks to enhance self-efficacy to ‘sit less, move more, and sleep better.’ Each week, the stepping goal will be increased according to the previous week’s activity level and the participant’s baseline activity. For instance, if the participant averaged 1000 steps daily at baseline, the focus of the coaching and recommended strategies will be to increase steps to 1500 steps daily over the next week, depending on the participant’s ability. Based on the participant’s progress, the stepping goal will be incrementally increased up to 6000 steps per day over 6 weeks. Following the Canadian Movement Guidelines of 7–9 hours of good quality sleep [30], sleep time will also be discussed and strategies to optimize sleep included in the goals for each week, such as establishing a routine bedtime schedule or avoiding screen-based activities about 30–60 minutes before bedtime.

**Fig 2 pone.0290515.g002:**
[figure not shown]
Examples of movement-related behaviours before and after a behaviour change program.

Participants in the BIG-STEPS arm will also wear a step counter on their ankle (Fitbit Inspire, Alphabet Inc., USA) [31] for self-monitoring, daily feedback and to monitor adherence. If a participant is discharged from the hospital before 6 weeks, we will complete the follow-up visits at the discharge location or virtually (where applicable).

## Control group: Usual care intervention

Participants allocated to the control group will receive usual inpatient and early supported discharge care (for those discharged early from hospital) in accordance with the Canadian Stroke Best Practices Guidelines [28]. This can include therapeutic mobilization directed by physical therapists or general mobilization directed by nursing staff, as tolerated. The specific exercises and treatments chosen for therapy will be up to the discretion of the therapy team. Study staff will document details regarding therapy sessions and any related issues. Participants in the usual care group will complete all assessments, including activity monitoring with the activPAL at the same time points as the experimental group.

### Randomization

Prior to the intervention, participants will be randomized on a 1:1 ratio, stratified by age (<60 or ≥60 years) and sex (male or female) to either the intervention or usual care group using computer-generated permuted random block sizes of 2 or 4 on a web-based platform (studyrandomizer.com).

### Blinding

Allocation will be fully concealed and completed by a blinded study team member not involved in data collection. Outcomes assessors will be blinded to group allocation.

## Data collection and management

Participant demographic, vital signs, and clinical characteristics, including stroke risk factors, infarct location and volume, and acute stroke treatments received (e.g. thrombectomy) will be determined and documented confidentially using the Research Electronic Data Capture (REDCap) register. Access to the register will be limited to authorized personnel. Data collection is currently ongoing.

### Outcomes

Feasibility outcomes will be assessed including safety and adverse events, reach, retention/attrition, and adherence/intervention fidelity as outlined in Table 1. Other outcomes will include global disability assessed using the validated 6-item modified Rankin Scale (mRS) that is a valuable end point for RCTs of acute ischemic stroke trials [32]. Functional mobility will be assessed using the Timed Up and Go (TUG) test, validated in people with stroke, with a minimal detectable change of 3.53 seconds [33,34]. Time spent in movement-related behaviours (sleep, sedentary behaviour, and physical activity) will be measured with activPAL accelerometer also validated in people with stroke [27]. Additionally, self-reported sleep quality will be assessed with the widely used Pittsburgh Sleep Quality Index [35]. Gait speed will be assessed with 10-Meter Walk Test, with a change of 0.16 meters/second in comfortable gait speed considered clinically important early poststroke [36,37]. Walking endurance will be tested with the 6-Minute Walk Test, with a minimal detectable change (MDC) of 54.1 meters poststroke [38]. The reliable and widely used National Institute of Health Stroke Scale (NIHSS) [39] will be used to classify stroke severity, and the Montreal Cognitive Assessment (MOCA) to assess cognitive impairment with good predictive value in acute stroke [40]. Quality of life will be assessed using the Euro-QOL 5D (EQ-5D) validated in people with stroke [41].

**Table 1 pone.0290515.t001:** Feasibility metrics.

**Feasibility**	Safety/adverse events Reach (recruitment, refusal rates) Retention/attrition rates Adherence/intervention fidelity	Record of any adverse events (i.e. falls) Number enrolled/number eligible, including refusal % enrolled who complete the study Record flow of participants through the study

MRI imaging will be collected only at baseline. Cortical infarct volume and leukoaraiosis will be determined from MRI scans, analyzed using standardized automated segmentation protocol of fluid-attenuated inversion recovery sequences, independent of demographic or clinical data.

We will report protocol deviations and the study data will be examined for outliers, normality and missing data. Identifying potential sources of missing data is essential for mitigating these issues in a definitive trial.

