### Statistical analysis

Participant baseline characteristics will be compared using independent t tests (continuous variables) or Chi-Square test (categorical variables). The Shapiro-Wilk test will be used to check for normality. Feasibility measurements (safety, reach, retention, adherence) will be calculated. Changes in functional mobility and global disability, movement-related behaviours, functional and quality of life outcomes across time (baseline to immediately post intervention to follow-up) will be determined using mixed-effects models. Compositional associations between movement-related behaviours and functional outcomes will be analyzed using compositional data analysis. We will consider the moderating effect of cortical infarct volume and leukoaraiosis on outcomes.

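### Mean sleep time has no direction of benefit when the programme aims for a 7-9 hour range, so a range-based sleep-duration measure should be pre-specified beside it

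*Protocol article*

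**What the plan says.** The Experimental group section of the protocol article ties the sleep part of the coaching to a range: "Following the Canadian Movement Guidelines of 7–9 hours of good quality sleep". Sleep time is discussed with the participant and strategies enter the weekly goals, for example "establishing a routine bedtime schedule or avoiding screen-based activities about 30–60 minutes before bedtime". No direction of change is stated.

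The Outcomes section defines the device-measured variable as time: "Time spent in movement-related behaviours (sleep, sedentary behaviour, and physical activity) will be measured with activPAL accelerometer". The next sentence adds a second sleep outcome: "self-reported sleep quality will be assessed with the widely used Pittsburgh Sleep Quality Index".

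The Statistical analysis section assigns "movement-related behaviours, functional and quality of life outcomes across time" to mixed-effects models of change. The compositional analysis in the same section relates behaviours to functional outcomes; it is not described as estimating the effect of the programme on sleep.

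Two statements in the background bear on how sleep time would be read. In the team's earlier cohort, "half of the participants have long sleep durations exceeding 9 hours per day". And, on the 24-hour day, "dedicating more time to physical activity necessitates reducing time spent sleeping or engaging in sedentary behaviour, or both".

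**The concern.** Sitting less and moving more each have one direction of benefit, so a mean difference in sedentary or stepping time can be read directly. Sleep duration with a two-sided target cannot. A participant at 10 hours reaches the target by sleeping less, and one at 6 hours by sleeping more. In a model of mean time these two successes have opposite signs.

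A mean that does move is also ambiguous. By the protocol's own displacement argument, a fall in average sleep could come from long sleepers entering the range, or from short and in-range sleepers giving up sleep for activity. The first meets the programme's aim and the second does not.

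What is at stake is the interpretation of one of the three named components. As written, the duration result cannot show whether the sleep-duration goal was met.

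**Working it through.** **The plan's own figures.** No figure is stated for sleep. The sample size rests on the Timed Up and Go: 45 participants for power 0.81, and 45/0.9 = 50 after 10% attrition, which reproduces. The power of 0.81 can be neither reproduced nor refuted, because no SD or correlation is given, and nothing below depends on it. I take only 45/2 = 22.5 per arm from it.

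**Inputs.** From the documents: the range 7-9 h, half of the earlier cohort above 9 h, and 1:1 allocation. Assumed: the share of short sleepers, the spread of sleep times, and how far the programme moves people.

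**Algebra.** Let E be the mean hours above 9 and S the mean hours below 7, averaged over all participants. If the programme closes a fraction f of each gap:

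- change in mean sleep time = f(S - E)
- change in mean distance from the range = -f(S + E)

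The mean responds to the difference between the two groups, the distance to their sum.

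**Fixed pull of 1 h, half above 9 h.** Let s be the share below 7 h, with everyone out of range at least 1 h from it. The mean changes by -0.5 + s and the distance by -(0.5 + s).

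- s = 0: mean -0.50 h, distance -0.50 h
- s = 0.25: mean -0.25 h, distance -0.75 h
- s = 0.5 (nobody in range): mean 0 h, distance -1.00 h

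**Ambiguity of a fall.** Take 50% at 10 h, 25% at 6 h and 25% at 8 h. The 1 h pull gives a mean change of 0.5(-1) + 0.25(+1) = -0.25 h. If instead everyone loses 0.25 h to activity, the mean change is again -0.25 h. Distance separates the two cases: -0.75 h in the first; in the second 0.5(-0.25) + 0.25(+0.25) = -0.0625 h.

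**Spread-out sleep times.** Normal distributions with SD 1 to 2.5 h were simulated, with each person outside 7-9 h moved to the nearest limit (f = 1) or half-way (f = 0.5) and controls unchanged. Approximate power = Φ(|Δ|/√((V_control + V_treated)/22.5) - 1.96). This counts rejections in one direction only, so it equals 0.025 at zero shift; the two-sided test rejects at 0.05.

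| Assumed centre | f | Mean shift (h) | Power, mean | Distance shift (h) | Power, distance |
|---|---|---|---|---|---|
| 8 h | 1 | 0.00 | 0.025 | -0.17 to -1.15 | 0.61-0.98 |
| 8.5 h | 1 | -0.17 to -0.35 | 0.09-0.11 | -0.23 to -1.19 | 0.72-0.98 |
| 9 h (half above 9 h) | 1 | -0.39 to -0.70 | 0.24-0.37 | -0.41 to -1.30 | 0.91-0.99 |
| 8 to 9 h | 0.5 | 0.00 to -0.35 | at most 0.11 | -0.08 to -0.65 | 0.17-0.47 |

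The f = 1 rows are optimistic for distance, because they put every treated participant inside the range. The f = 0.5 row is the more sober comparison.

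**The case against.** Several stronger readings are tempting, and the documents do not support them.

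- A reader might infer that a working programme could show no effect on sleep at all. The Pittsburgh Sleep Quality Index is a planned outcome, and the named strategies are general sleep-hygiene measures, so quality may improve whatever happens to hours. The point is confined to mean sleep time. The index is self-reported and does not measure whether duration reached the range, so it does not replace a duration measure.
- A reader might infer that the mean will be null. The only figure available, half above 9 h, points to a net fall. With a 1 h pull, exact zero needs the entire other half below 7 h. The figure also comes from people returning to the community after inpatient rehabilitation, not from patients within 7 days of onset.
- A reader might infer that the protocol states an aim to shorten long sleep, or contradicts itself. It does neither. The two-sided aim follows from the range, and each statement is true taken alone.

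It can also be said that derived accelerometer variables belong in an analysis plan that is not shown, and that sleep time is one of many other outcomes in a 50-person trial that lists feasibility first and is sized on the Timed Up and Go. That limits the weight of the point. It does not remove the mismatch between the stated target and the stated metric.

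Finally, raw sleep time has its own use: it shows displacement within the 24-hour day and is needed for the composition, whereas distance from a range does not sum to 24 hours. This stands, and is a reason to add a measure and not to replace raw hours. For the same reason the compositional models need no change.

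**Conclusion.** The concern holds for mean device-measured sleep time. With a 7-9 hour target, the planned metric has no direction of benefit. A programme that brings people into range would probably show a diluted effect on the mean, and none only if short and long sleepers balance. With half above 9 h and a 1 h pull, the mean change lies between -0.5 and 0 h, against -0.5 to -1.0 h in distance. If there are no short sleepers the two are equal in size, and only the ambiguity of sign remains. At about 45 analysed participants, power for the mean is at most 0.37 in the scenarios run, and at most 0.11 if the programme closes half the gap. Distance does better throughout, but reaches only 0.17-0.47 in the half-gap case.

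These sizes rest on assumed sleep distributions, an assumed pull and unchanged controls. The lack of a readable sign does not rest on them; it follows from the target and the metric. No stated decision rule depends on sleep hours, so this affects the reading of one component and not the trial as a whole.

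**What to change.** Keep raw sleep time for description and for the compositional analysis. Beside it, pre-specify one range-based variable as the measure by which the sleep-duration goal is judged:

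- hours outside 7-9 h: 0 inside the range, otherwise the distance to the nearest limit; or
- the share of participants within 7-9 h.

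Analyse it in the same mixed-model framework with arm, visit and their interaction (a logistic version for the share). State whether the distance is taken from the weekly average or night by night, since the two differ for irregular sleepers. Many values will be zero, so use robust or bootstrap standard errors. Report over-sleep and under-sleep separately, because distance alone loses direction.

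The cost is a derived variable and a few sentences of analysis text; no new visit, device or participant is needed. Data collection is already under way, so the choice should be recorded before any data are examined by arm. Made later, it would be post hoc.
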